#### Palliative Prognostic Index (PPI)

The PPI uses PPS and four bedside parameters to predict a probabilistic short-term survival of terminally ill cancer patients, from 0 to 15 (i.e. likelihood of being alive at 3 and 6 weeks). A total score over 6 predicts a survival of less than 3 weeks [37, 38]. The PPI may be sufficient to evaluate prognosis in cases where laboratory values are not available [39]. Limitations of the PPI include the difficulty of accurately diagnosing delirium and its low negative predictive value.

#### Support Team Assessment Schedule (STAS)

STAS provides a score from 0 (*best*) to 4 (*worst*) to assess a patient’s symptom burden [40]. The reliability, validity and inter-rater reliability of the Japanese version have been confirmed [41, 42].

#### European Organisation for Research and Treatment of Cancer (EORTC) Quality of Life Questionnaire Core 15 Palliative care (QLQ-C15-PAL)

The EORTC QLQ-C15-PAL will be used to assess the patient’s QOL [43]. The EORTC QLQ-C15-PAL is a short version of the EORTC QLQ-C30; it consists of 15 items as a core questionnaire for palliative care settings. The global QOL item is rated from 1 (*very poor*) to 7 (*excellent*), and the others are rated from 1 (*not at all)* to 4 (*very much*). The reliability and validity of the Japanese version have been confirmed [44].

### Procedures

#### Enrolment and allocation

Patients hospitalised in PCUs will be screened for eligibility. Eligible patients will be informed of the study procedure, data protection plan, risks, and benefits by investigators. In the RCT arm, each patient who agrees to participate and provides written consent will be randomly allocated to either the intervention group (Op-reha Guide) or the control group (usual rehabilitation). The patients in the RCT arm will start rehabilitation within 7 days after hospitalisation. In the observation group, each patient who agrees to participate and provides written consent will start observation within 7 days of hospitalisation; they will not be randomly allocated.

Data on eligible patients who have given informed consent will be collected and managed using a web-based electronic data capture system in the Japanese Organisation for Research and Treatment of Cancer (JORTC) Data Centre. We used a computer-generated randomisation schedule using stratified permuted block randomisation methods to assign patients to either the intervention or control group in a 1:1 ratio, balanced for the following stratification factors: 1) ECOG PS is 2 or 3; and 2) study site.

#### Blinding

This study follows a single-blind design. In the RCT arm, we will not provide information to patients as to which of the two protocol treatments is based on the Op-reha Guide and which is based on usual rehabilitation. Hence, patients will be blinded to the intervention, but the therapists and other collaborators will be unblinded.

#### Data collection

Assessments will be performed at five time points: enrolment (T0 eligibility and randomisation), Day 1 (T1 baseline), Day 8 (T2), Day 15 (T3), and Day 22 (T4) by investigators consistently at each site. The Day 1 assessment is performed on the day rehabilitation begins in the RCT arm, and on the hospitalisation day within 7 days in the observation group. If a patient is discharged or withdraws before T4, a withdrawal assessment will be performed. If a patient continues to be hospitalised after withdrawal, the remaining measurements will be performed according to the assessment schedule. The follow-up assessment is performed 30 days after T4 or withdrawal. The timing and details of assessments are given in Table 1.

**Table 1 Tab1:** Study procedure and time points for actions and evaluations

	T0 Enrolment	T1 Day1 Baseline	T2 Day 8	T3 Day 15	T4 Day 22	Discharge or Withdrawal	Follow-up30 days after T4 or discharge/ withdrawal
Demographics		x	x	x	x	x	
mBI		x	x	x	x	x	
EORTC QLQ-C15-PAL		x	x	x	x	x	
ECOG PS	x	x	x	x	x	x	
PPS		x	x	x	x	x	
STAS	x	x	x	x	x	x	
PPI	x	x					
Adverse events (RCT)		x	x	x	x	x	
Details of the rehabilitation (RCT)			x	x	x	x	
Reason for stopping (RCT)						x	
Clinical outcome							x

*mBI* modified Barthel Index, *EORTC QLQ-C15-PAL* European Organisation for Research and Treatment of Cancer Quality of Life Questionnaire Care 15 Palliative Care, *ECOG PS* European Cooperative Oncology Group Performance Status, *PPS* Palliative Performance Scale, *STAS* Support Team Assessment Schedule, *PPI* Palliative Prognostic Index, *RCT* Randomised Controlled Trial

### Interventions

The specialised rehabilitation according to the Op-reha Guide and usual rehabilitation will be administered for 3 weeks in the RCT arm by rehabilitation therapists. After the study is completed or the patient withdraws, rehabilitation and care according to this study protocol will end, and the patient will receive the site’s usual treatment. As study participation is voluntary, the patients can any time withdraw from the study.

#### Op-reha Guide

The Op-reha Guide is a newly developed intervention guide for rehabilitation therapists designed to address the need to maintain the ADL of terminal cancer patients hospitalised in PCUs. It was developed by integrating both the experience of clinical practice and the literature review by the multidisciplinary team. The team consisted of a rehabilitation therapist (OT and PT), a nurse, a clinical psychologist, and three physicians specialising in palliative care. We also included the opinions of other rehabilitation therapists with expertise in palliative care. The core concepts of the Op-reha Guide are: 1) to optimise the actions and attitude of rehabilitation therapists according to the patient’s needs and condition; 2) to share the goals with the patient; 3) to implement rehabilitation designed to maintain ADL. The Op-reha Guide consists of 22 recommended actions in total; the basic length is 40 min per day, with a frequency of five times per week to adequately perform the actions.

To increase adherence to the protocol intervention and reduce the risk of contamination, we take some measures with the operation method of the Op-reha Guide as follows. First, we will prepare a detailed operational procedure manual and explain the manual in detail for the site investigators at the kick-off meeting, instead of providing training. Only the therapist in charge of patients allocated to the intervention group will be able to access the guide and only for the duration of their intervention. Next, the therapist will receive a recommended list of set actions for each implementation day, with a checklist that must be filled out after each treatment. The therapists may treat both intervention and control group patients but cannot be in charge of the two groups at the same time.

#### Usual rehabilitation as control

Currently, there is no specific standard rehabilitation for terminal cancer patients hospitalised PCU in Japan. Thus, we defined the basic length as 20 min per day, five times per week, which is the average rehabilitation length and frequency for cancer patients hospitalised PCUs in Japan according to the most frequent response in a questionnaire survey conducted in Japan [45].

#### Usual care (observation group)

The observation group will receive usual care without specialised rehabilitation during hospitalisation. Usual care will be provided to all patients by physicians, nurses, and allied health professionals without rehabilitation therapists.

### Study endpoints

We hypothesise that the intervention group will more effectively maintain their ADL than the control group. Therefore, we selected ADL as the primary endpoint and chose QOL as one of the secondary endpoints.

The primary endpoint is the change in total mBI from baseline to T4. The secondary endpoints are as follows: 1) change in total mBI from baseline to T3/T2; 2) change in each sub-item score of mBI from baseline to T4/T3/T2; 3) longitudinal change in total and sub-item scores of mBI at baseline, T2, T3, and T4; 4) proportion of patients who show a decrease of 10 points or more in total mBI from baseline to T4/T3/T2; 5) change in each domain score of EORTC QLQ-C15-PAL from baseline to T4/T3/T2; and 6) adverse events in the RCT arm.

### Analysis

#### Data management and monitoring

All data will be collected by the JORTC Data Centre, which will also oversee the intra-study data sharing process. The clinical data entry, data management, and central monitoring will be conducted using the electronic data capture system REDCap (developed by Vanderbilt University, USA).

#### Study population for analyses

The population for efficacy and safety analyses comprises all patients who receive at least one session of the protocol intervention. Patients who are found to be ineligible after registration will be excluded from the efficacy analysis, although they will be included in the safety analysis (adverse events).

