### Participants and setting

Participants will be recruited from 16 PCUs across Japan. There will be 11 PCUs in the RCT arm and 5 PCUs in the observation arm, and participants will be enrolled according to the inclusion and exclusion criteria. Inclusion criteria are: a) an initial hospitalisation in PCU; b) being 20 years or older at the time when they provide informed consent; c) having a clinical diagnosis of cancer; d) receiving no curative treatment, such as surgery, radiation therapy, or chemotherapy; e) European Cooperative Oncology Group Performance Status (ECOG PS) of 2 or 3; f) having a clinically estimated life expectancy of 3 weeks or more (based on the opinion of investigators and Palliative Prognostic Index of 6 or less); g) starting specialised rehabilitation within 1 week of hospitalisation in PCU (only RCT arm); and h) having the ability to provide written informed consent. Exclusion criteria are: a) having a severe symptom burden (i.e. score of 4 on any of the three Support Team Assessment Schedule items of pain control, other symptom control, and patient anxiety); b) having a respite admission within 1–2 weeks; c) having a weight-bearing limitation due to impending bone fracture; and d) will be undergoing a nerve block anaesthesia or percutaneous vertebroplasty (cement composition).

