#### Statistical analysis

Comparison of the primary endpoint (i.e. mean difference in the change in total mBI from baseline to T4) between the intervention group and control group will be conducted using a two-sided one-way *t*-test with a significance level of 5% according to the intention-to-treat principle. Point estimates and 95% confidence intervals for the mean difference between the two groups will be calculated. This analysis will also be conducted between the control group and observation group. For supplementary analysis that compares the control and observation groups, a multivariate analysis will be conducted with the primary endpoint as the dependent variable, and groups and background information as independent variables. The secondary endpoints of efficacy will be evaluated similarly. For the safety evaluation, the frequency and incidence of adverse events for each group will be calculated. A full statistical analysis plan will be written prior to the data evaluation. All analyses will be performed using SAS version 9.4 (SAS Institute, Cary, NC, USA).

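### The efficacy set (at least one session received, patients later found ineligible removed) is not the intention-to-treat set that the primary comparison is said to follow

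*Protocol article*

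**What the plan says.** Two adjacent sections of the protocol article fix who enters the primary analysis.

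- Study population for analyses sets a treatment condition: "The population for efficacy and safety analyses comprises all patients who receive at least one session of the protocol intervention". It adds an eligibility condition: "Patients who are found to be ineligible after registration will be excluded from the efficacy analysis". Ineligible patients stay in the safety analysis.
- Statistical analysis specifies a two-sided t-test of the change in total mBI from baseline to T4, "with a significance level of 5% according to the intention-to-treat principle". The same analysis is to be run between the control and observation groups.

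Four other sections bear on this.

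- Data collection and Table 1 place eligibility and randomisation at T0 and the baseline at Day 1 (T1). In the RCT arm, Day 1 is the day rehabilitation begins. Table 1 schedules mBI from T1 onwards, not at T0.
- Blinding says that patients are blinded while therapists and other collaborators are not.
- Inclusion criterion (g) in Participants and setting is worded "starting specialised rehabilitation within 1 week of hospitalisation in PCU (only RCT arm". Enrolment and allocation gives the same limit as a procedure: "The patients in the RCT arm will start rehabilitation within 7 days after hospitalisation".
- Usual care (observation group) says: "The observation group will receive usual care without specialised rehabilitation during hospitalisation".

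**The concern.** Intention-to-treat analysis keeps every randomised patient in the allocated group. A set that requires a session and removes patients on a later eligibility finding does not. The article does not call this set modified, and it defines no all-randomised set. Two statisticians could each follow one of the two sections and analyse different patients.

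The point matters because both exclusions happen after allocation, among staff who know it. In a terminal population, patients who never reach a first session may well be those who deteriorate or die early. If such patients, or patients judged ineligible later, are lost at different rates in the two arms, the primary comparison loses part of the protection of randomisation. The article states no safeguard, such as eligibility review blind to allocation or limited to facts that existed before randomisation.

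The observation group raises a related difficulty. It receives no protocol session, so the one-session rule cannot define its efficacy set, yet it is to be compared with the control group.

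**Working it through.** **1. The two rules side by side**

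| Randomised patient | Study population for analyses | Intention-to-treat |
|---|---|---|
| Eligible, at least one session | analysed | analysed |
| Eligible, no session | not analysed | analysed |
| At least one session, later found ineligible | not analysed for efficacy | analysed |
| No session, later found ineligible | not analysed | analysed |

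The rules agree in the first row only.

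**2. The plan's own figure** (Sample size calculation: difference 10, SD 15, two-sided 5%, power 80%, attrition 15–20%)

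n per arm = 2 × (1.96 + 0.84)² × 15² / 10² = 35.3, rounded up to 36.

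36 / 0.85 = 42.4, so 43; 36 / 0.80 = 45. The stated 45 per group, 90 in total, is reproduced at 20% attrition.

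**3. Possible bias.** The documents give no exclusion rate, so every input here is an assumption. Let a fraction f of an arm be excluded, and let those patients change D mBI points worse than the patients retained. Then

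bias in (intervention − control) = f_I × D_I − f_C × D_C.

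If only one arm loses patients, its size is f × D:

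| f (of 45) | D = 10 | D = 20 | D = 30 |
|---|---|---|---|
| 2% (about 1 patient) | 0.2 | 0.4 | 0.6 |
| 5% (about 2) | 0.5 | 1.0 | 1.5 |
| 10% (4 to 5) | 1.0 | 2.0 | 3.0 |

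This is 2–30% of the 10-point target. The sign depends on which arm loses the patients. With equal f and D in both arms the bias is zero.

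**4. Effect on type I error** (no true difference, 36 analysed per arm, SD 15)

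SE = 15 × √(2/36) = 3.54. Rejection probability = 1 − Φ(1.96 − b/SE) + Φ(−1.96 − b/SE):

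- b = 1: 5.9%
- b = 2: 8.7%
- b = 3: 13.6%

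**5. Effect on power of exclusions on top of attrition**, with n = 45 × (1 − attrition) × (1 − exclusion) and power = Φ(10 / (15√(2/n)) − 1.96):

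| Attrition | no exclusion | 5% excluded | 10% excluded |
|---|---|---|---|
| 15% | 83.0% | 81.1% | 79.0% |
| 20% | 80.7% | 78.7% | 76.5% |

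**6. Can a patient who never starts be analysed?** In the RCT arm Day 1 is the day rehabilitation begins, and mBI is first scheduled that day. A randomised patient without a session therefore has no scheduled baseline mBI, and no Day 1 from which to count to Day 22. Widening the set on paper yields no change score for that patient. A treated patient later found ineligible does have a baseline and can be retained at once.

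**The case against.** The strongest reply is that the one-session rule applies alike to both randomised groups, since both receive protocol rehabilitation, and largely coincides with having a baseline mBI. On this view the avoidable loss is mainly of treated patients later found ineligible. Removing ineligible patients can be acceptable if it rests on pre-randomisation facts judged blind. A full analysis plan was still to be written. Most of this stands, and it limits what can be said about size. It does not reconcile the two sections: each fixes a rule, and a later plan cannot satisfy both.

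Several stronger readings are tempting, but the documents do not support them.

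- **That this is an as-treated analysis.** Nothing moves patients to the group whose treatment they received. The set is compatible with analysis as allocated among those who remain.
- **That a late start makes a randomised patient ineligible under criterion (g).** Eligibility is assessed at T0, and the 7-day limit also appears as a procedure. No section says that a late start is later counted as ineligibility. The wording is loose, no more.
- **That delay will differ by arm** because sessions are 40 versus 20 minutes and a therapist may not be in charge of both groups at once. The therapist rule is symmetric, and nothing links session length to the date of the first session.
- **That sites will decide ineligibility knowing the allocation.** The article does not say who decides. It states neither a site-level decision nor a safeguard.
- **That the observation group is to be deleted.** Statistical analysis compares it with control and Sample size calculation plans 45 patients for it. The defect is an undefined set.

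**Conclusion.** The contradiction is certain from the text: the defined efficacy set is a treated-and-eligible set, and the stated principle is intention-to-treat. Bias that depends on allocation is possible, because both exclusions follow randomisation, staff are unblinded and no blinded review is stated. It is not shown. Its size and direction cannot be derived from the documents. The 0.2–3.0 point range assumes exclusions in one arm only, of 2–10%, with 10–30 points of excess decline; a few balanced exclusions would change little.

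In the control versus observation comparison, keeping the one-session rule for control alone would select control patients who reach a first session, with no matching condition on the other side. That comparison is non-randomised in any case, and the Discussion acknowledges that participant characteristics may differ.

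The sets should be corrected before the data are evaluated, because they decide who enters the primary analysis.

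**What to change.** 1. Define the primary efficacy set as all randomised patients analysed as allocated, including those later found ineligible. Keep the treated-and-eligible set, under that name, for sensitivity analysis.
2. Record baseline mBI at T0, or state how randomised patients who never start rehabilitation enter the analysis. Without one of these, item 1 cannot be carried out for them.
3. At minimum, retain treated patients later found ineligible, or allow removal only on pre-randomisation facts judged blind to allocation.
4. Clarify that criterion (g) is judged at T0 as a planned start.
5. Define a separate set for the observation group, with the same entry point for control and observation patients in that comparison.

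The cost is rewording, possibly one earlier mBI assessment, and slight dilution of the estimate by patients who never start. The RCT sample size stays at 90 (45 per group).

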#### Statistical analysis

Comparison of the primary endpoint (i.e. mean difference in the change in total mBI from baseline to T4) between the intervention group and control group will be conducted using a two-sided one-way *t*-test with a significance level of 5% according to the intention-to-treat principle. Point estimates and 95% confidence intervals for the mean difference between the two groups will be calculated. This analysis will also be conducted between the control group and observation group. For supplementary analysis that compares the control and observation groups, a multivariate analysis will be conducted with the primary endpoint as the dependent variable, and groups and background information as independent variables. The secondary endpoints of efficacy will be evaluated similarly. For the safety evaluation, the frequency and incidence of adverse events for each group will be calculated. A full statistical analysis plan will be written prior to the data evaluation. All analyses will be performed using SAS version 9.4 (SAS Institute, Cary, NC, USA).

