#### Sample size calculation

To calculate the sample size for the RCT arm, we assumed that the mean difference in the change in total mBI from baseline to T4 would be 10 (standard deviation, 15) between the groups. There was no previous study on the minimal clinically significant difference (MCID) in mBI at the planning stage of this study. Thus, we decided to adopt a 10-point difference compared with usual rehabilitation as the MCID of this study by extrapolating the MCID of the 20-point scale of the BI [46]. Assuming a 15–20% attrition rate, we calculated 90 patients (45 patients in each group) with a two-sided significance level of 5% and a power of 80%. We decided that the sample size of the observation group would also be 45 patients.

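### The primary t-test on mBI change to Day 22 is labelled intention-to-treat but is undefined for patients who die first, and it uses none of the earlier mBI values the trial collects

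*Protocol article*

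**What the plan says.** - **Endpoint** (Study endpoints): "The primary endpoint is the change in total mBI from baseline to T4". T4 is Day 22.
- **Test** (Statistical analysis): the groups are compared on the "mean difference in the change in total mBI from baseline to T4" with a "two-sided one-way *t*-test with a significance level of 5% according to the intention-to-treat principle". The secondary efficacy endpoints are to be handled in a similar way, and a full statistical analysis plan is announced.
- **Eligibility** (Participants and setting): "having a clinically estimated life expectancy of 3 weeks or more", based on investigator opinion together with a PPI of 6 or less. The section on the PPI says that scores above 6 predict survival under three weeks, and lists a low negative predictive value among its limitations.
- **Early exit** (Data collection): "If a patient is discharged or withdraws before T4, a withdrawal assessment will be performed". Scheduled visits continue after withdrawal only while the patient stays in hospital. Death is not mentioned. Table 1 shows mBI collected at T1, T2, T3, T4 and at discharge or withdrawal, and clinical outcome at the 30-day follow-up.
- **Sample size** (Sample size calculation): "mean difference in the change in total mBI from baseline to T4 would be 10 (standard deviation, 15) between the groups", and then "Assuming a 15–20% attrition rate, we calculated 90 patients (45 patients in each group".
- **Secondary endpoint 4** (Study endpoints): "proportion of patients who show a decrease of 10 points or more in total mBI", from baseline to T4, T3 or T2.

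**The concern.** A t-test on change to Day 22 needs a Day 22 value from every patient it compares. The article gives no value, rank or composite for a patient who dies first. The survival floor for entry is about as long as the interval to the endpoint, so these deaths are part of the expected course of the trial. They are also tied to the outcome: the Background says that ADL falls in the last one to three months of life.

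If the test is applied to observed T4 values, the frailest patients leave the comparison. When they leave at different rates, the arm that loses more of them looks better on function. The intention-to-treat label then no longer describes what is compared. Live discharge is a second route out, and it need not act in the same direction.

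The trial collects mBI at T2, T3 and withdrawal. These values carry information on patients without a T4 value, but they enter only secondary endpoints or, for the withdrawal value, no stated analysis. Secondary endpoint 4 has the same gap, since nothing says whether a death counts as a decline.

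**Working it through.** **1. Reproducing the plan's own figure.** Inputs from Sample size calculation: difference 10, SD 15, two-sided 5%, power 80%, attrition 15–20%.

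n per group = 2 × (1.960 + 0.842)² × 15² / 10² = 2 × 7.85 × 2.25 = 35.3, so 36.

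With 20% attrition: 36 / 0.80 = 45 per group, 90 in total. This matches the plan. With 15% attrition: 36 / 0.85 = 42.4, so 43 per group. At 36 per group, power is 80.7% by the normal approximation and 79.7% by the t distribution. The size is sound on its own terms. Inflation restores the number of values; it does not address which patients supply them.

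**2. Timing.** Day 1 to Day 22 is 21 days, and the entry floor is an estimated three weeks. The documents give no expected Day 22 mortality, so none is asserted here.

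**3. Size of the selection effect if only observed T4 values are used.** The SD of 15 comes from the plan. The correlation ρ between change in mBI and a latent survival variable, and the loss rates, are assumptions. If a fraction a with the lowest latent survival has no T4 value, the mean change among those left is shifted upward by

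s(a) = ρ × 15 × φ(z_a) / (1 − a), where z_a is the a-quantile of the standard normal.

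- a = 0.10: 15 × 0.1755 / 0.90 = 2.92, times ρ
- a = 0.20: 15 × 0.2800 / 0.80 = 5.25, times ρ
- a = 0.40: 15 × 0.3863 / 0.60 = 9.66, times ρ

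The bias in the group difference is the difference of these shifts. It favours the arm with more loss. The rejection rates come from 3,000 simulated trials per setting with 45 per arm and no true effect (simulation error about 0.4 percentage points at 5%).

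| Loss, arm A / arm B | ρ = 0.3 | ρ = 0.5 | ρ = 0.7 | Rejection at nominal 5% |
|---|---|---|---|---|
| 20% / 20% | 0 | 0 | 0 | 4.4–4.6% |
| 20% / 10% | 0.7 | 1.2 | 1.6 | 5.8–7.9% |
| 40% / 20% | 1.3 | 2.2 | 3.1 | 6.3–13.8% |

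For scale, the planned difference is 10 and its standard error with 36 per arm is 15 × √(2/36) = 3.5.

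**4. Why the rule for death matters.** Suppose baseline mBI is 60 and survivors fall by 20 (both assumed). A death scored as mBI 0 is a change of −60, which is 40 points worse than a survivor. Ten percentage points more deaths in one arm then move the difference by 0.10 × 40 = 4 points against that arm, while the observed-values analysis moves 0.7 to 1.6 points in its favour. These are different estimands, and the article does not say which one it intends.

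**The case against.** The strongest reply is that the article nowhere prescribes a complete-case analysis. It is a condensed account, a full analysis plan is announced, and missing-data handling normally belongs there. A t-test can also follow imputation or use a substituted withdrawal value. This stands as far as it goes: a reader might infer that patients who die are dropped, but that is an inference. Inflating for attrition does not prove it either, since inflation is compatible with imputation or a longitudinal model. What remains is that the endpoint, the test and the intention-to-treat label are already fixed in the article, and together they are undefined for a foreseeable group of patients.

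A reader might also infer that a patient who only just qualifies will be dead by Day 22, all the more because rehabilitation may start up to seven days after admission. The documents do not support this. The criterion is a minimum and an estimate. The PPI is scored at enrolment and again on Day 1, and nothing starts the three-week estimate at admission.

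Discharged patients are not without data: mBI is taken at discharge or withdrawal, and T2 and T3 feed secondary endpoints. The point is only that the primary test uses none of these.

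For secondary endpoint 4, a t-test does not literally fit a proportion, so similar handling cannot settle the denominator. The article does not say that deaths are left out; it does not say either way.

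Finally, the illustrated bias is small against a planned difference of 10, and it needs unequal or differently informative loss, which no section predicts. That is correct and limits the claim. A repeated-measures model is also no complete answer, because it implicitly extrapolates function beyond death.

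**Conclusion.** The point holds in a limited form. The primary analysis does not say what happens to patients who die before Day 22, although the eligibility criteria make such deaths foreseeable, and as written it ignores relevant mBI data that the trial collects. Run on observed T4 values, it compares survivors still under assessment, which is not what its label promises.

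Bias in the group difference is conditional. It is zero with equal and similarly informative loss, and 0.7 to 1.6 mBI points for loss of 10% versus 20% at correlations of 0.3 to 0.7. Both the loss rates and the correlations are assumptions. A reader might conclude that the result is bound to be biased or to have the wrong sign; the documents do not show that, and a reversed sign would need a true effect smaller than the bias. Nor is the sample size in error: 90 is correct under the stated 20% attrition.

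**What to change.** Before data evaluation, in the protocol or analysis plan:

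1. Replace the T4-only t-test with a baseline-adjusted repeated-measures model for mBI at T2, T3 and T4. Include all randomised patients with data and keep the group difference at T4 as the primary contrast. Enter the withdrawal assessment at its nearest scheduled visit, with a rule for when that visit already has a value.
2. State explicitly how death before T4 is treated in the primary estimand.
3. Pre-specify a sensitivity analysis with death before T4 as the worst outcome (mBI 0 or worst rank).
4. In secondary endpoint 4, count death as a decline of 10 points or more and keep deaths in the denominator.
5. Report deaths and live discharges by arm beside the primary result.

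The cost is wording and some analysis time, since the mBI data are already being collected and no more patients are needed. There are two downsides. The model assumes that data are missing at random and implicitly extrapolates mBI after death, which is why items 2 and 3 are needed alongside it. The death-as-worst analysis with mBI 0 will have a larger SD and so less precision.

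### The primary t-test on change in mBI is valid but does not condition on baseline mBI or the randomisation strata, so it may give up precision that costs almost nothing to keep

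*Protocol article*

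**What the plan says.** Study endpoints defines the outcome: "The primary endpoint is the change in total mBI from baseline to T4", T4 being Day 22. Statistical analysis then fixes the test as a t-test on the change score. Its wording for the comparison is "between the intervention group and control group will be conducted using a two-sided one-way", where the name of the test comes next. The level and the analysis principle are given as "with a significance level of 5% according to the intention-to-treat principle". A point estimate and 95% confidence interval for the mean difference are to be reported. No covariate is named. The only model with covariates in that section is the supplementary comparison of the control group with the non-randomised observation group. Secondary efficacy endpoints are to be handled in a similar way.

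Enrolment and allocation describes randomisation in stratified permuted blocks, "balanced for the following stratification factors: 1) ECOG PS is 2 or 3; and 2) study site". Table 1 shows mBI measured at the Day 1 baseline. Participants and setting gives 11 sites in the randomised part.

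Sample size calculation assumes that the mean difference in change "would be 10 (standard deviation, 15) between the groups". It continues: "Assuming a 15–20% attrition rate, we calculated 90 patients (45 patients in each group"), with two-sided 5% significance and 80% power.

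**The concern.** Subtracting baseline is not the same as conditioning on it. The change score assumes that the slope of Day 22 mBI on baseline mBI is exactly 1. If the slope differs from 1, change still depends on baseline, the residual variance is larger than it need be, and part of any chance baseline imbalance stays in the estimate.

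Stratified randomisation raises a second issue. Blocking balances ECOG PS and site between the groups, so the true sampling variance of the difference falls if those factors are prognostic. An unadjusted t-test still counts their variation as noise, and its standard error is then too large.

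At stake is precision, in a trial planned with almost no power in reserve and in patients who are hard to recruit and retain. Although a full statistical analysis plan is promised, the article has already chosen the primary test, so this is a comment on a stated choice and not on a missing detail.

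**Working it through.** **Inputs from the article:** difference 10, SD of change 15, two-sided 5%, 80% power, attrition 15–20%, 45 per arm, 11 sites × 2 ECOG PS levels = 22 strata.

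**Assumed, because the article does not give them:** the correlation r between baseline and Day 22 mBI; the ratio k = SD at Day 22 / SD at baseline; the site and ECOG PS effects; the block size.

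**1. The planned sample size.** Per arm, n = 2 × (1.960 + 0.842)² × 15² / 10² = 35.3, rounded up to 36. With 20% attrition, 36 / 0.80 = 45 per arm, 90 in total. The stated figure reproduces, and it is sized for the unadjusted test.

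**2. Unadjusted power.** The standard error is 15 × √(2/36) = 3.54 and the noncentrality is 10 / 3.54 = 2.83. Power is 80.7% by the normal approximation and 79.7% by the noncentral t on 70 df. With 15% attrition (about 38 per arm), the noncentral t gives 81.8%.

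**3. Adjusting for baseline mBI.** The variance of the adjusted estimate relative to the change-score estimate is

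k²(1 − r²) / (1 + k² − 2rk),

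which reduces to (1 + r)/2 when k = 1. The slope of Day 22 on baseline is rk. The residual SD is 15 × √ratio. Power is at 36 per arm, by the noncentral t on 69 df.

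| k | r | slope | ratio | residual SD | power |
|---|---|---|---|---|---|
| 1 | 0.5 | 0.50 | 0.75 | 12.99 | 89.6% |
| 1 | 0.6 | 0.60 | 0.80 | 13.42 | 87.7% |
| 1 | 0.7 | 0.70 | 0.85 | 13.83 | 85.7% |
| 1 | 0.8 | 0.80 | 0.90 | 14.23 | 83.6% |
| 1 | 0.9 | 0.90 | 0.95 | 14.62 | 81.6% |
| 1.1 | 0.8 | 0.88 | 0.97 | 14.76 | 80.9% |
| 1.25 | 0.5 | 0.63 | 0.89 | 14.17 | 83.9% |
| 1.25 | 0.8 | 1.00 | 1.00 | 15.00 | 79.6% |
| 1.4 | 0.7 | 0.98 | 1.00 | 15.00 | 79.7% |

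The gain disappears as the slope approaches 1. Even there, the cost is one degree of freedom, which is less than 0.1 points of power.

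**4. Baseline imbalance.** If the groups differ by b points at baseline, the unadjusted difference in change shifts by (slope − 1) × b. With r = 0.8 and k = 1, that is −0.2 points per point of imbalance.

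**5. The strata.** A simulation used 11 sites × 2 ECOG PS levels, blocks of 4, 72 evaluable patients, a total SD of change of about 15, and r = 0.5 or 0.8. Each scenario had 4,000 runs under no effect and 2,000 with a difference of 10. The full model had baseline mBI, ECOG PS and fixed site terms.

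| Site ICC, ECOG PS effect | t-test type I error | full-model type I error | t-test mean CI width | full-model mean CI width |
|---|---|---|---|---|
| none | 4.7–4.9% | 5.1–5.6% | 14.1 | 12.7–13.9 |
| 0.05, 5 points | 4.2–4.5% | 5.1–5.3% | 14.1 | 12.2–13.3 |
| 0.10, 5 points | 4.0–4.3% | 5.0–5.3% | 14.0 | 11.8–13.0 |
| 0.20, 10 points | 2.9% | 4.8–5.2% | 13.9–14.0 | 10.5–11.5 |

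The Monte Carlo standard error at a 5% rate is √(0.05 × 0.95 / 4000) = 0.3 points. With no stratum effects and r = 0.8, simulated power was 79.8% for the t-test, 83.0% with baseline alone and 80.5% for the full model. Fixed site terms that predict nothing can therefore use up most of the gain from baseline.

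**The case against.** The strongest reply is that nothing is broken. Endpoint, test and sample size all use the change score, the planned number follows from them, and an unadjusted comparison under randomisation is unbiased. All of that stands. What remains is forgone precision.

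Several stronger readings are tempting, and the article does not support them:

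- **Inflated false-positive risk.** Ignoring the strata errs the other way. In the simulation the t-test's type I error never exceeded 5%.
- **Chance baseline imbalance passing straight into the estimate.** That would describe raw Day 22 scores. With a change score, only the fraction (slope − 1) passes through.
- **A guaranteed gain, such as 40 to 48 effective patients per arm for 36.** Those figures are 36/0.90 and 36/0.75, so they need equal SDs and r between 0.8 and 0.5. The article reports neither SD nor r. The Background describes ADL decline in the last months of life, so the spread may change by Day 22. With k = 1.25 and r = 0.8 the effective number stays at 36.
- **An undefined test.** *One-way* is the wrong word, but two groups, a two-sided level and a mean difference with its interval identify a two-sample t-test. This is editorial.

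The Discussion also expects confounders to be adjusted for. It says so when explaining the choice of individual over cluster randomisation, and it does not specify an adjusted analysis of the randomised groups.

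**Conclusion.** The point holds as a matter of efficiency and not of validity. The primary t-test conditions on neither baseline mBI nor the stratification factors. Where those predict change, it gives up precision, and for the strata its interval is conservative.

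For baseline adjustment alone, power at 36 evaluable per arm moves from 79.7% to between no gain and about 90%. The range 81.6–89.6% applies for r from 0.9 to 0.5 with equal SDs, and the gain vanishes when the slope is near 1. The further effect of ECOG PS and site depends on how prognostic they are, and could be nil. That no covariate is named is certain; the size of the gain is not, because it rests on quantities that the article does not report. Since the downside is about one degree of freedom for baseline and a few for the strata, the change is worth making.

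**What to change.** Before group data are examined, replace the primary analysis with a linear model of change in total mBI (or mBI at Day 22) on group, baseline mBI and ECOG PS (2 or 3). Include site as a random effect, or pool small sites: 22 strata across about 72 evaluable patients is roughly three per stratum, too few to spend a fixed term on every site. Report the adjusted mean difference with its 95% confidence interval at the two-sided 5% level.

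Keep the unadjusted comparison as a sensitivity analysis and call it a two-sample t-test. Use the same model, with the corresponding baseline score, for the continuous secondary endpoints.

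The cost is a sentence or two in Statistical analysis, carried into the statistical analysis plan. The sample size need not change, and no extra patients or measurements are required.
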